**Suspected *HSR***



- Present case of suspected HSR to on-site study clinician before patient leaves clinic
- Determine if ABC needs to be discontinued. (Note: A patient will only continue on ABC if syndrome is likely to be of another etiology and the patient is available for close follow-up)
- Place patient on “ABC HSR Evaluation and Follow-up Protocol” (Section 8.1.2.2.3)
- Report suspected HSR on ABC HSR Reporting form or Serious Adverse Event form as clinically indicated within one business day of event

Final Diagnosis of ABC HSR for Analysis

At the stage of classification, HSR is defined as a clinical syndrome with findings from two or more of the following groups of signs or symptoms occurring simultaneously in a patient receiving ABC:

- Fever > 38°C
- Rash
- One or more gastrointestinal symptoms (nausea, vomiting, abdominal pain, diarrhea) occurring while treating with Trizivir
- One or more respiratory symptoms not directly referable to active TB: dyspnea, non-productive cough, sore throat
- One or more systemic musculoskeletal symptoms: myalgia, arthralgia (involving multiple joints)
- One or more neurologic symptoms: severe headache, paresthesias not attributable to INH

**AND**

Exclusion of the following conditions as a cause of the symptom complex:

- Chemical (especially rifampin) or viral hepatitis
- Gout, arthritis or arthralgias caused by pyrazinamide
- Exacerbation of underlying tuberculosis
- Immune reconstitution syndrome (IRIS) to TB (paradoxical reaction)
- HIV-related condition such as cryptococcal meningitis, oral thrush, esophageal candidiasis, cryptosporidiosis/microsporidiosis, etc.

**AND**

Resolution of symptoms with the discontinuation of ABC. Resolution of symptoms within 48 to 72 hours will constitute the strongest evidence for HSR

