##### 6.3.1.2.1 Hypersensitivity Reaction (HSR) associated with Abacavir (ABC)

In clinical studies, approximately 3%-5% of patients receiving ABC develop an HSR that in rare cases has proved fatal. HSR is characterized by the appearance of symptoms indicating multi-organ/body system involvement. Symptoms usually appear within the first 6 weeks of starting treatment with ABC (median time to onset is 11 days), but may occur at any time while on therapy.

This section describes the diagnostic criteria that will be operationalized in the study. The clinical management of the syndrome is described under Clinical Management (Section 8.1.2.2.3). In this protocol we will distinguish the clinical diagnosis made at the time of evaluation from the final classification of a suspected HSR that will be used in the analysis. The clinical diagnosis will be made by the study team on-site using information available at the time of the evaluation. For the analysis, the Clinical Review Committee will examine all available data including the clinical course after ABC is withdrawn. This later classification will be used in the analysis of the study.

Clinical Diagnosis of ABC HSR

The diagnosis of HSR will be suspected when a patient receiving ABC presents to a routine or sick visit with a combination of fever, rash, gastrointestinal symptoms, worsening respiratory symptoms, neurologic symptoms. Although there is no diagnostic test available to confirm the clinical diagnosis of HSR, a routine medical evaluation will be performed including vital signs and physical examination looking for clinical characteristics of HSR. Standard laboratory evaluation will include CBC with differential count, serum chemistries, creatinine, and liver function tests. If liver enzymes are abnormal, then viral serologies for hepatitis A and B will be drawn.

Because the signs and symptoms of HSR are non-specific, and may be confused with side effects of rifampin, other HIV conditions, or paradoxical reactions, the evaluations of these patients will be as extensive as possible to allow for accurate diagnosis at the time of the event and proper classification for analysis.

HSR is defined as a clinical syndrome with findings from two or more of the following groups of signs or symptoms occurring simultaneously in a patient receiving ABC:

- Fever > 38°C
- Rash
- One or more gastrointestinal symptoms: nausea, vomiting, abdominal pain, diarrhea

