### **Immune Reconstitution Inflammatory Syndrome (IRIS) to TB**

### **(Paradoxical Reactions)**

Immune Reconstitution Inflammatory Syndrome (IRIS) to TB(paradoxical reactions) are defined as (1) new persistent fevers (temperature  38.6C) which develop after the initiation of HAART and which last for more than 1 week without an identifiable source (e.g., urine and sputa testing, and other procedures when clinically indicated); OR (2) marked worsening or emergence of intrathoracic lymphadenopathy, pulmonary infiltrates; OR (3) worsening or emergence of cervical adenopathy on serial physical examinations, OR worsening of other tuberculosis lesions or manifestations, such as cutaneous peritoneal or central nervous system (CNS) inflammatory pathology. (Appendix VI)

All cases of suspected paradoxical reaction will be reviewed in a blinded way by the Clinical Review Committee (see Section 5.2.3) and classified for analysis. Since it will not be possible to differentiate HSR from paradoxical reaction, some cases will be classified as having both syndromes.

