# 10.0 STATISTICAL CONSIDERATIONS

## 10.1 Sample Size

In this randomized clinical trial we will enroll a total sample size of 350 HIV-infected TB patients into Step 2 with 175 randomized to punctuated therapy and 175 randomized to anti-TB treatment only and delayed ARV therapy. The sample size was estimated to provide a power of 80 – 90% to detect an effect size of 35% or greater for HIV disease progression. This effect size translates into an average delay of about one year before the need to start ARV therapy. The sample size will not include patients who enter Step 1 but are not eligible to progress to Step 2.

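### The analysis definition of abacavir hypersensitivity shuts out a death without prior symptom resolution, and its IRIS exclusion conflicts with section 6.3.3

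*Protocol*

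**What the plan says.** Section 6.3.1.2 of the protocol treats specific adverse reactions as study outcomes. Section 6.3.1.2.1 separates the on-site clinical diagnosis of HSR from a final classification made by the Clinical Review Committee, and says of the latter: "This later classification will be used in the analysis of the study".

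Under the final diagnosis for analysis, three elements are joined by AND:

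1. Findings from at least two symptom groups at the same time.
2. "Exclusion of the following conditions as a cause of the symptom complex". The list includes IRIS to TB (paradoxical reaction).
3. "Resolution of symptoms with the discontinuation of ABC. Resolution of symptoms within 48 to 72 hours will constitute the strongest evidence for HSR".

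The same section gives the background risk: "In clinical studies, approximately 3%-5% of patients receiving ABC develop an HSR that in rare cases has proved fatal".

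Section 6.3.3 sends suspected paradoxical reactions to the same committee for classification and adds: "Since it will not be possible to differentiate HSR from paradoxical reaction, some cases will be classified as having both syndromes".

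**The concern.** Two problems follow from reading these rules as written.

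First, the third element makes resolution a requirement. Only its timing (48 to 72 hours) is graded as strength of evidence. No exception is given for a patient who dies before symptoms resolve, so the definition has no place for a kind of outcome that the section itself says has occurred.

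Second, the committee holds two rules for the same event. Section 6.3.1.2.1 makes exclusion of IRIS as the cause a condition for HSR. Section 6.3.3 says the two cannot be differentiated and expects some cases to carry both labels. Where they truly cannot be differentiated, the exclusion cannot be met.

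At stake is the adjudicated HSR tally, including its fatal cases, that the safety aim (Specific Aim 3) would report for the punctuated regimen. If the rule is left open, it would have to be settled after the cases are known.

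**Working it through.** The protocol states no expected HSR count and no power for HSR, so there is no figure to reproduce. The check is of logic first, then of scale.

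**Fatal case.** Take a patient with two symptom groups, the listed causes excluded, and death before any resolution. Elements 1 and 2 are met and element 3 is not. Because the elements are joined by AND, the case is not HSR for analysis.

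**Case in which IRIS cannot be excluded as the cause.** Under 6.3.1.2.1, element 2 fails and the case is not HSR. Under 6.3.3, the case is classified as both. The two results differ and neither section says which governs.

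**Is the overlap practical?** Median HSR onset is 11 days after starting ABC (6.3.1.2.1), which is 11/7 = 1.6 weeks. IRIS typically appears 1–3 weeks after starting antiretrovirals (8.1.2.2.8). The windows coincide, and 6.3.1.2.1 itself warns that HSR may be confused with paradoxical reactions.

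**Scale.** Inputs from the protocol: 175 patients assigned to the ABC-containing arm (10.1); HSR in 3–5% (6.3.1.2.1); IRIS in up to one third on potent antiretrovirals (8.1.2.2.8); paradoxical reactions in 36% with and 7% without antiretrovirals (1.1.2). Any ABC used after the primary outcome is left out.

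Assumptions, not in the protocol: HSR and IRIS are independent; the IRIS frequency is used as the share of HSR cases in which IRIS cannot be excluded, with 7% as a low illustration; case fatality of HSR is 0.1%, 1% or 5%, since the protocol says only that it is rare.

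- Expected HSR cases = 175 × rate: 175 × 0.03 = 5.25; 175 × 0.05 = 8.75.
- Cases that turn on the IRIS rule = expected HSR × overlap. Expected fatal cases = expected HSR × case fatality.

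| | HSR 3% | HSR 5% |
|---|---|---|
| Expected HSR cases | 5.25 | 8.75 |
| Turn on IRIS rule, 7% overlap | 0.37 | 0.61 |
| Turn on IRIS rule, one-third overlap | 1.75 | 2.92 |
| Turn on IRIS rule, 36% overlap | 1.89 | 3.15 |
| Expected fatal, 0.1% case fatality | 0.005 | 0.009 |
| Expected fatal, 1% case fatality | 0.05 | 0.09 |
| Expected fatal, 5% case fatality | 0.26 | 0.44 |

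If 6.3.1.2.1 governed and 36% of cases were excluded, the counted rate would be 3% × 0.64 = 1.9% to 5% × 0.64 = 3.2%, instead of 3–5%. At 7% overlap it would be 2.8% to 4.7%. With so few cases, one reclassification moves the expected count by 1/8.75 = 11% to 1/5.25 = 19%.

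**The case against.** A reader might infer that HSR is under-reported by construction and that the trial's safety conclusion is compromised. The documents do not support that, for several reasons that stand.

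- **Capture is separate.** Every suspected HSR goes on its own form (6.3.1), ABC hypersensitivity is reported as a serious adverse event (8.1.2.2.3), and so is every death (6.1.3). The between-arm comparison in 10.2.2.3 is of grade III/IV adverse reactions and paradoxical reactions. It names no HSR rate.
- **Fatal HSR is not zero by definition.** Section 8.1.2.2.3 describes deaths after ABC is reintroduced. A patient whose first episode resolved off ABC and who died on rechallenge can qualify through that first episode. Severe HSR that resolves is also counted.
- **Loss to IRIS is not certain.** Cases drop out only if 6.3.1.2.1 overrides 6.3.3, which no text says. The exclusion concerns IRIS as the cause of the episode, so HSR with a separate IRIS event can still carry both labels.
- **The overlap figures are crude.** Section 1.1.2 calls the frequency of paradoxical reactions unknown. IRIS at any time is not the same as IRIS that cannot be excluded as the cause of one episode. An IRIS fever must last more than a week (6.3.3), while rapid resolution favours HSR, so some cases will separate.
- **The direction is open.** The symptoms are non-specific, and all antiretrovirals are held when HSR is strongly suspected (8.1.2.2.3). Resolution is therefore not specific to ABC, and false positives are possible.

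It can also be said that the committee reviews all available data. That does not answer the point: three elements joined by AND give it no stated way to classify these cases.

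**Conclusion.** The concern holds in limited form. The final definition cannot classify as HSR a patient who dies of it without any prior resolution, and its IRIS exclusion cannot be reconciled with 6.3.3 for cases that are truly indistinguishable. The effect is confined to the adjudicated HSR count and HSR fatality count.

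About 5 to 9 HSR cases are expected among 175 patients. Between about 0.4 and 3 depend on which IRIS rule is followed, given independence and 7–36% overlap. Fewer than one fatal case is expected at every case fatality assumed. The fatal-case gap matters because the event is grave, not because it is likely.

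The primary endpoint and the planned Aim 3 grade III/IV comparison are untouched, and the net direction of bias is not established. This is a definition worth correcting before adjudication. It is not a defect that must be cured for the trial to answer its main question.

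**What to change.** Amend the final diagnosis for analysis in 6.3.1.2.1:

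- **Deaths.** State that a case meeting the symptom and exclusion criteria, in which the patient dies before resolution can be judged, is classified by the Clinical Review Committee as probable HSR. List other cases with unevaluable resolution separately and do not count them as HSR by default. Otherwise, lost patients with two non-specific symptoms would inflate the count.
- **IRIS.** Reconcile the exclusion list with 6.3.3 by making HSR/IRIS not distinguishable an explicit category, and refer to it in both sections.
- **Reporting.** Give definite HSR alone; definite, probable and indistinguishable together; and all suspected cases.

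The protocol already grades recurrent TB by certainty (6.2.6), so the approach is familiar to the committee. The cost is amendment wording and added categories on the committee form, with no new data. The downside is that the broader count is less specific. Clinical management of suspected HSR is unchanged.

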##### 6.3.1.2.2 Severe Anemia

Grade 3 anemia is defined as a hemoglobin level between 6.5 and 6.9 g/dl. Grade 4 anemia is defined when the hemoglobin < 6.5 g/dl.

##### 6.3.1.2.3 Elevated Liver enzymes

Grade 3 elevation in liver enzymes is defined as a serum AST level > 5 to 10 times the upper limit of normal. Grade 4 elevations in liver enzymes is defined as a serum AST level > 10 times the upper limit of normal.

### **6.3.2 Development of ARV drug resistance**

Viral drug resistance will be examined in specimens from patients with confirmed failure to suppress HIV RNA < 200 copies/ml after the six month course of antiretroviral therapy on step 2 or after six months of antiretroviral therapy on Step 3, and, for a random subset of 20 patients 2 months after completing punctuated therapy. In these patients, pre-treatment plasma will also be assayed for drug resistance. Genotypic analysis performed at the Joint Clinical Research Center Virology laboratory will be used to evaluate for drug resistance. Resistance will be defined according to IAS/USA guidelines.

### **Immune Reconstitution Inflammatory Syndrome (IRIS) to TB**

### **(Paradoxical Reactions)**

Immune Reconstitution Inflammatory Syndrome (IRIS) to TB(paradoxical reactions) are defined as (1) new persistent fevers (temperature  38.6C) which develop after the initiation of HAART and which last for more than 1 week without an identifiable source (e.g., urine and sputa testing, and other procedures when clinically indicated); OR (2) marked worsening or emergence of intrathoracic lymphadenopathy, pulmonary infiltrates; OR (3) worsening or emergence of cervical adenopathy on serial physical examinations, OR worsening of other tuberculosis lesions or manifestations, such as cutaneous peritoneal or central nervous system (CNS) inflammatory pathology. (Appendix VI)

All cases of suspected paradoxical reaction will be reviewed in a blinded way by the Clinical Review Committee (see Section 5.2.3) and classified for analysis. Since it will not be possible to differentiate HSR from paradoxical reaction, some cases will be classified as having both syndromes.

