A prescribed drug interruption raises the concern that HIV resistant virus will be selected. In our study, the risk for drug resistance will be minimized because patients will be ARV therapy naïve, will receive a potent triple combination regimen (not a single drug like nevirapine), and will receive a form of directly observed therapy. Several studies have shown that effective viral suppression can be achieved when re-instituting ARV therapy after treatment interruption in naïve patients with initial viral suppression. Nevertheless, recognizing the importance of looking for drug resistance, a secondary objective of our study is to monitor for the presence of resistance as a part of the overall assessment of the punctuated therapeutic strategy.

Benefit of ARV Therapy on response to TB treatment

ARV therapy in HIV-infected patients with active TB may have beneficial effects on the response of patients to antituberculous therapy. Improvement and/or augmentation of host responses to mycobacterial antigens after treatment with ARV therapy is supported by two lines of evidence. First, in our studies of responses to MAC, and in similar studies of responses to PPD in BCG vaccinated patients, in vitro proliferative responses to mycobacterial antigens were restored 3-6 months after initiation of ARV therapy. Second, the frequency of "paradoxical reactions" in HIV-infected patients undergoing treatment of tuberculosis is much higher in patients who are treated with antiretroviral therapy (36%) versus those who are not (7%). The rapid onset of these reactions and response to prednisone suggest heightened immune activation and responsiveness to mycobacterial antigens.

Improved host immune responses may also hasten clearance of MTB from the sputum. Although not studied for MTB, for other opportunistic infections, ARV can speed clearance of the pathogen or resolution of the syndrome.53 Resolution of cryptosporidiosis, microsporidiosis, progressive multifocal leukoencephalopathy (PML), *M. avium* bacteremia and Kaposi Sarcoma after the initiation of ARV provide evidence that improving immune function can lead to improved outcome in an acute opportunistic infection.54-56 More rapid clearance of MTB has implications not only for the patient but also for transmission to susceptible contacts.

Relevance of Antiretroviral Interventions in Uganda

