**5.0 STUDY PHASES: STUDY ENTRY, INTERVENTION AND POST-OUTCOME**

##

## 5.1 Study Entry – Step 1

All patients in this study will receive routine treatment for tuberculosis (see Section 5.1.1). The experimental intervention in this study is the use of punctuated antiretroviral therapy for six months during treatment for tuberculosis. Because standard anti-TB drugs represent the background treatment, these drugs will not be considered study drugs. When patients have been found to be eligible for the study and have given informed consent, all patients will be started on antituberculosis treatment, given daily for a total of six months and will have the following baseline assessment:

1. Informed consent for study
2. Medical history and physical examination, including weight
3. HIV RNA Roche Amplicor
4. PBMC storage/ immune function (Flow cytometry to assess cell surface activation markers, EliSpot to assess CD4 and CD8 T cell specificity to HIV and microbial peptides, Whole blood assays to determine antigen specific response to HIV and microbial antigens)
5. Plasma & Buffy Coat storage

Patients will be evaluated weekly while in Step 1. At one week from study entry all patients will be assessed for readiness to start on the Trizivir-based punctuated ARV therapy with the following evaluation:

1. Medical history and physical examination, including weight
2. New Diagnosis and hospitalization survey
3. Adverse event survey
4. Pregnancy test (urine or serum *β*-HCG)
5. Complete blood count with differential
6. Liver function tests (AST and serum bilirubin)
7. Serum creatinine
8. Adherence to antituberculosis therapy
9. Quality of life survey
10. Disease specific diagnostic tests

The patient will be scheduled to return to the clinic 1 week after this evaluation (two weeks after the start of TB therapy) to be randomized or identified as having contraindications (see Section 4.4). If the patient has contraindications to starting the Trizivir-based ARV intervention they will be scheduled to return to the clinic in another week (Week 3) and be reassessed.

Thus, all patients evaluated at week 1 will be scheduled to return to the clinic at week 2, and may be randomized or reassessed for randomization at that time; those patients that have contraindications at week 2 may be scheduled to return to the clinic for randomized or reassessment at week 3; and those patients reassessed at week 3 will be scheduled to return to the clinic and may be randomized at week 4.

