### **8.1.2 Toxicity Management**

#### **8.1.2.1 General Guidelines for Adverse Experiences Associated with HIV and ARV**

#### **Therapy**

##### 8.1.2.1.1 Grades 1 and 2

Subjects who develop a Grade 1 or 2 adverse event or toxicity may continue study drugs without alteration of the dosage, except **as stated in the following sections**.

In general, for grade 1 toxicities, the patient should be followed carefully, and the study drug should be continued. The patient will receive specific counseling about the observed toxicity and will be instructed on what to do if symptoms worsen. For grade 2 toxicities, the patient should be followed carefully, with additional laboratory and/or clinic appointments as clinically indicated, and the study drug or combination held at the local clinician’s discretion until the event has resolved. The clinician should also evaluate concomitant medications to determine whether to withhold or discontinue the study drugs. Guidelines for the discontinuation of study drug is given in (Section 8.1.4.2).

Grade I and II events will be reported on standard case report forms.

##### 8.1.2.1.2 Grades 3 and 4

For any grade III or IV adverse event or toxicity, the offending agent(s) or all potential causative agents will be held pending evaluation. When clinically indicated, concomitant medications should be held first if the local clinician suspects they are contributing to the toxicity. In many instances, however, all study drugs will be discontinued at once to reduce risk to the patient. The on-site clinical coordinator will report the grade IV events to the study investigators and the Data and Statistical Center within 24 hours using standard procedures; the Data and Statistical Center will be responsible for reporting the grade IV event to the study sponsor. Grade III and IV adverse events and toxicities as defined by the Study Toxicity Tables (Appendices IV and V) and occurring during study therapy or within 60 days of the last study dose must be documented as Adverse Events. The standard reporting level for adverse events will be followed, reporting only grade IV events to the Division of AIDS.

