#### **10.2.2.3 Specific Aim 3**

To determine whether a punctuated six-month course of highly active ARV therapy is safe when given with anti-tuberculosis therapy as measured by development of ARV drug resistance, toxicity and side effects, and paradoxical reactions.

Safety

The safety of the study interventions, including adverse events and paradoxical reactions will be examined by summarizing the proportion, or rate, of these events according to each study arm. We will compare the cumulative proportion of grade III/IV adverse reactions and paradoxical reactions between study arms with the chi-square or Fisher’s exact test. Time until first event will also be examined using Kaplan-Meier analysis with log-rank test to compare arms. Because an individual may have more than one adverse event, we will also estimate the incidence density of adverse events in each study arm and compare these rates by determining the relative risk of adverse events (with 95% confidence intervals) in the group receiving intervention compared with the reference group.

Viral drug resistance

Descriptive analyses of drug resistance mutations in reverse transcriptase will be performed. Based on HIV RNA patterns and values, samples will be assayed from patients who exhibit viral rebound during the punctuated therapy phase and, for a subset of 20 patients 2 months after completing punctuated therapy. If resistance is identified in samples off therapy, we will assay the plasma for persistence of the mutations. We will also assess drug resistance in all specimens from patients who exhibit virologic failure (confirmed HIV RNA >200 copies/mlafter 6 months of therapy, Section 8.1.3) during the continuation phase (Step 3). Proportions and rates of drug resistance will be compared between the 2 strategies.

Analysis of Additional Outcomes

Analysis when CD4+ < 250/µL and Continuous ARV Therapy Begun

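### The persistent-fever criterion for a paradoxical reaction can be met only after ARV therapy starts, so the planned between-arm comparison is uneven for fever-only reactions

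*Protocol*

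**What the plan says.** Section 6.3.3 defines a paradoxical reaction by alternatives joined by OR, and Appendix VI repeats them:

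- Limb (1) is new persistent fever, limited to fevers "which develop after the initiation of HAART and which last for more than 1 week without an identifiable source".
- Limb (2) is "marked worsening or emergence of intrathoracic lymphadenopathy, pulmonary infiltrates". It carries no condition on ARV therapy.
- Limb (3) is "worsening or emergence of cervical adenopathy on serial physical examinations", or worsening of other tuberculous lesions. It also carries no condition on ARV therapy.

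Section 6.3.3 adds that all suspected cases are "reviewed in a blinded way by the Clinical Review Committee".

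For Aim 3, section 10.2.2.3 says: "We will compare the cumulative proportion of grade III/IV adverse reactions and paradoxical reactions between study arms", by chi-square or Fisher's exact test. Time to first event is to be compared by log-rank test. Table 4 in section 5.2.1.1 gives the delayed arm anti-TB drugs only during the intervention period.

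On grade III and IV events, section 8.1.2.1.2 says that those "occurring during study therapy or within 60 days of the last study dose must be documented as Adverse Events". Section 5.1 says: "Because standard anti-TB drugs represent the background treatment, these drugs will not be considered study drugs".

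**The concern.** In the months when the arms differ, the same fever in the same week of TB treatment can be an outcome event in the punctuated arm and cannot be one in the delayed arm. The protocol itself expects reactions without ARV therapy, since section 1.1.2 gives 7% for untreated patients against 36% for treated ones. Fever is also not a marginal sign: section 8.1.2.2.8 names it with worsening lymphadenopathy as the most common manifestation. A comparison under this wording therefore mixes a real effect of ARV therapy with an effect of the definition.

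The wording also conflicts with blinding. To apply limb (1), the committee must know whether and when ARV therapy began, and before Step 3 that amounts to knowing the arm.

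The grade III/IV wording raises a related but weaker question. If only ARV drugs are study drugs, the documentation window covers about eight months in the punctuated arm (six months plus 60 days) and does not exist in the delayed arm before Step 3.

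**Working it through.** The protocol gives no figure for this point, so there is none to reproduce. The check has three parts.

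**1. Which limbs each arm can meet before Step 3**

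| Limb | Punctuated arm | Delayed arm |
| --- | --- | --- |
| (1) persistent fever | yes, once ARV therapy starts | no |
| (2) intrathoracic nodes, infiltrates | yes | yes |
| (3) cervical nodes, other TB lesions | yes | yes |

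Only reactions that qualify through limb (1) alone are lost in the delayed arm. A fever accompanied by worsening nodes or infiltrates still counts in both arms.

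**2. Size of the distortion**

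Inputs:
- n = 175 per arm (section 10.1).
- Two-sided alpha of 0.05. The protocol states it for the primary calculation (Figure 5 legend); it is assumed here for the safety test.
- Reaction rates of 36% with and 7% without ARV therapy (section 1.1.2).
- f, the share of delayed-arm reactions that are fever-only. The protocol does not give it. It is assumed to be 0.25, 0.50 or 0.75.

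If the true rates are p1 (punctuated) and p2 (delayed), the recorded delayed-arm rate is p2(1 − f). The recorded risk ratio is p1 / [p2(1 − f)], so the true ratio is multiplied by 1/(1 − f).

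*At the protocol's own rates* the true ratio is 0.36/0.07 = 5.1:

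- f = 0.25: 0.36/0.0525 = 6.9
- f = 0.50: 0.36/0.035 = 10.3
- f = 0.75: 0.36/0.0175 = 20.6

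Power for 36% versus 7% with 175 per arm exceeds 99.9%. In this case the wording changes the estimate, not whether a difference is found.

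*With equal true rates of 7%* the exact rejection probability is obtained by summing over all outcomes of Binomial(175, 0.07) and Binomial(175, 0.07(1 − f)), rejecting when the uncorrected chi-square exceeds 3.84. The normal approximation is Φ[(d − 1.96·s0)/s1] + Φ[(−d − 1.96·s0)/s1]. Here d is the difference in recorded rates, and s0 and s1 are its pooled and unpooled standard errors.

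| f | Recorded delayed rate | Recorded ratio (true 1) | Rejects, exact | Rejects, normal approx. |
| --- | --- | --- | --- | --- |
| 0 | 7.0% | 1.00 | 4.9% | 5.0% |
| 0.25 | 5.25% | 1.33 | 10.1% | 10.5% |
| 0.50 | 3.5% | 2.0 | 30.7% | 31.1% |
| 0.75 | 1.75% | 4.0 | 70.3% | 67.2% |

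The row f = 0 is the position once both arms face the same criterion.

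**3. Grade III/IV events, passages side by side**

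- Definition: sections 6.3, 6.3.1.2.2 and 6.3.1.2.3 and Appendix IV grade events by toxicity tables and laboratory cut-offs. None refers to ARV therapy.
- Documentation: the section 8.1.2.1.2 window refers to study therapy and the last study dose, and section 5.1 excludes anti-TB drugs from the study drugs.
- Capture in both arms: section 6.3.1.1 requires serious events to be reported for study subjects throughout the study, and section 6.3.1 counts grade 4 events as serious. Sections 7.3.2 and 7.3.3 schedule adverse-event surveys in Step 2 without distinction by arm.

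What remains exposed is non-serious grade III events in the delayed arm.

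**The case against.** The strongest reply is that little of the safety comparison is affected. Limbs (2) and (3) are open to both arms. Section 8.1.2.2.8 and Appendix VI describe reactions in which fever comes with worsening nodes or infiltrates, and those already count in both arms, so a fever-only share as high as 75% has no support in the protocol. The equal-rate scenario departs from the 36% and 7% that the protocol cites. The error inflates apparent harm of the intervention and does not hide it, and the primary endpoint is untouched. All of this stands, and it limits the size and weight of the point. It does not remove the unequal criterion or the conflict with blinded classification.

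A reader might infer two stronger claims. The first is that only one arm can meet the paradoxical-reaction definition at all; limbs (2) and (3) rule that out. The second is that grade III/IV events are also defined by ARV exposure, so that their comparison is biased by design. The protocol does not support this either. Their definition is arm-neutral, section 6.3.1.2 makes reactions to anti-TB as well as ARV drugs study outcomes, and section 8.2.2.1 grades TB-related events on the same tables. Section 8.1.2.1.2 states what must be documented and excludes nothing from analysis. Section 8.2.3.2 uses the term study drug loosely for anti-TB drugs, so the strict reading of section 5.1 is possible but not established.

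**Conclusion.** The point holds for the fever limb. Before Step 3 a delayed-arm patient cannot meet it, so the section 10.2.2.3 comparison is asymmetric against the punctuated arm for fever-only reactions, and a committee blinded to arm cannot apply it.

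The direction is certain; the size is not. The inflation factors of 1.33, 2.0 and 4.0 rest on assumed fever-only shares. The false-positive rates of about 10%, 31% and 70% rest in addition on equal true rates of 7%. They illustrate the mechanism and are not forecasts for this trial.

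For grade III/IV events the finding is only an ambiguity: the documentation rule could be read as giving the delayed arm no mandatory window for non-serious grade III events. Overall severity is moderate, since this concerns one limb of a secondary safety outcome.

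**What to change.** 1. In section 6.3.3 and Appendix VI, for the between-arm analysis, make the fever limb run from randomization instead of from the start of HAART. Both arms then face the same criterion, and the committee can classify without knowing ARV exposure.
2. Report reactions that occur after Step 3 ARV therapy begins separately from the between-arm comparison.
3. In section 10.2.2.3, state that the grade III/IV comparison uses the same window from randomization in both arms, and align the documentation sentence in section 8.1.2.1.2 with it, so that non-serious grade III events are recorded equally.

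The cost is wording in the protocol and the case report form guidance. The visits and adverse-event surveys needed are already scheduled for both arms. The change is best made before suspected cases are classified, because fevers not recorded as suspected reactions in the delayed arm may not be recoverable later.
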